### Eligibility criteria for sex partners

Named as a sex partner of the index patient within the appropriate look back period (6 months for chlamydia, 3 months for PID, 1 month for NGU)^29^ and selected by the index patient for APT and aged 16 years or older.

### Intervention

The APT intervention is a complex intervention involving index patient, healthcare professional and sex partner, situated within wider clinical care (figure 1). In qualitative research studies to optimise the intervention, we explored the acceptability of individual components of the APT intervention with members of the public, sexual health clinic attenders and healthcare professionals.^30^ During the intervention phase, clinics will offer APT as an additional option for eligible patients, alongside standard PN, described in box 1 for index patients, and box 2 and figure 2 for sex partners. Eligible index patients who receive standard PN will receive the same follow-up as those who receive APT. If APT is no longer feasible (eg, sex partner unavailable), standard PN will be offered instead.

Box 1Overview of accelerated partner therapy (APT) for index patientsIndex patient has partner notification (PN) consultation with healthcare professional (HCP); HCP assesses eligibility for APT.Eligible index patient is offered APT alongside the clinic’s other standard PN options. The patient can choose different methods for different partners.Index patient telephones or messages sex partner (with or without the HCP present, according to preference) to offer immediate telephone assessment by the HCP.Index patient waits in clinic while the HCP conducts APT telephone consultation in private with sex partner.Index patient is informed that they will receive a follow-up telephone call in 2 weeks and they will either receive a chlamydia self-sampling postal kit in 12–16 weeks (preferred), or they may re-attend the clinic for testing.Two-week follow-up: research health adviser (RHA) telephones index patient to find out about PN outcomes with partner(s), to remind them of the repeat test, and to invite them to be contacted about taking part in a telephone interview regarding their experiences of APT (process evaluation).12 weeks: index patient is sent a personalised text reminder about repeat test.13 weeks: index patient is sent a self-sample kit by The Doctors Laboratory (TDL). Index patient returns self-collected sample or attends clinic for repeat testing. S/he receives results either via text message from TDL (negative results) or using routine clinic systems (positive or equivocal results). Positive results are managed according to routine clinic protocol. If the index patient does not return a self-sample or attend clinic for repeat testing, they receive a personalised text reminder 8 days after the self-sample kit is sent out, followed by a telephone call from the RHA 13 days after the self-sample kit is sent out. Self-samples received >24 weeks post-PN interview are excluded.

Box 2Overview of accelerated partner therapy (APT) for sex partnersIndex patient telephones sex partner to inform them about exposure to chlamydia and offer immediate telephone assessment (APT).If sex partner agrees to APT, healthcare professional (HCP) telephones them and conducts a clinical assessment in private. If appropriate, sex partner is offered an APT pack (delivered by the index patient or mailed directly). Sex partners for whom APT is inappropriate or who do not wish to continue with the APT option, will be advised by the HCP to attend clinic for further management. During the same telephone call, HCP invites sex partner to be contacted about taking part in a telephone interview regarding their experiences of APT (process evaluation).Sex partner receives APT pack (figure 2), which contains: antibiotics (either azithromycin or doxycycline, depending on local clinic practice); condoms; information about chlamydia, gonorrhoea, HIV and syphilis; chlamydia and gonorrhoea self-sampling kit, HIV and syphilis self-sampling kit, and information leaflet about how to take a sample (including link to an explanatory online video: lustrum.org.uk/test-and-treat); request form for the sample to be processed by the lab; envelope for return of self-sampling kits and APT pack packaging (envelope or small box, no branding or other identifiable markings, and which fits through standard letterbox).Sex partner completes self-sampling, labels and returns samples for testing.Sex partner takes antibiotic treatment.Sex partner informed of test results by text (negative results) or routine clinic processes; positive results are managed according to routine care.

**Figure 2 F2:**
[figure not shown]
Contents of sex partner accelerated partner therapy pack. Pack contains: antibiotics; condoms; Limiting Undetected Sexually Transmitted infections to RedUce Morbidity TEST & TREAT leaflet; vulvo-vaginal swab kit or urine sampling kit; blood sampling kit; instruction leaflet for sampling kits; test request form for sample processing; prepaid return post envelope; security seal sticker; attention card.

### Control

During the control phase, each clinic follows their usual protocols for standard PN. All clinics conduct enhanced patient referral, including verbal information about notifying partners plus additional information (written leaflets or signposting to a website). The healthcare professional will occasionally notify partners on behalf of the patient, if requested. Follow-up telephone calls and repeat testing will be the same as those during the APT phase.

### Outcomes

The primary clinical outcome is the proportion of index patients with a positive test result for *C. trachomatis* 12–16 weeks after the PN consultation. A repeated positive test result after treatment is a proxy for re-infection from an untreated partner, assuming that other reasons for a repeat positive test result are distributed equally between intervention and control arms. This outcome has been used in RCTs of PN interventions seeking to demonstrate prevention of transmission at the level of the individual.^16^

Secondary clinical outcomes are: (1) the proportion of sex partners treated 2 weeks after the initial PN consultation; (2) numbers of partners treated per index patient; (3) time to partner treatment and (4) number of patients notified per index patient. These outcomes will be ascertained by index patient reports at the 2-week follow-up telephone call with the research health adviser (RHA). Additional secondary outcomes include exploring the acceptability of the APT intervention to index patients and sex partners through qualitative telephone interviews with patients and partners as part of the process evaluation. We will determine rates of STI and HIV testing in sex partners and proportions of positive test results for STIs and HIV among sex partners who return postal self-sampling kits contained in APT packs. We will determine costs associated with the intervention in economic evaluation studies based on costings of the trial. We will record any adverse events using local activity logs at each trial site and report them to the trial sponsor and ethics committee.

### Sample size

The trial is designed to determine superiority of APT as an adjunct to standard PN compared with standard PN. Our calculation is based on recruiting an average of 160 index patients per clinic per trial phase from the 17 participating clinical services (total 5440 patients) and a coefficient of variation in the number recruited of 0.5. We expect that 50% of recruited patients (80 per clinic per phase and 2720 total) will contribute to the analysis of the primary outcome because we restrict this analysis to patients with *C. trachomatis* detected at baseline. We assume that 60% of index patients will provide a repeat sample for *C. trachomatis* detection and we expect that 10%–25% of patients in the control arm will have *C. trachomatis* detected at the 12–16 weeks follow-up.^16 31 32^ This sample size provides 80% power (at the 5% significance level) to detect a fall in *C. trachomatis* positivity from 10% to 5%, and 82% power to detect a fall from 25% to 17%. We consider such reductions would be reasonable if around half the index patients in the intervention phase select APT for some or all their partners, but our calculation does not assume any specific value of APT uptake. A period of 6 months in the control condition and 6 months in the intervention condition should be sufficient to reach this target. Related to our key secondary outcome (the proportion of sex partners treated), for simplicity, we consider power to detect an effect on the proportion of index patients with one or more partner treated. This sample size provides 87% power to detect an increase from 60% in the control arm to 70% in the intervention arm.^17^

Sample size calculations are guided by Giraudeau *et al*^33^ and performed as if the trial were a standard cluster RCT with 17 clinics in each arm. The cross-over design in our trial, with each cluster contributing data to both intervention and control conditions, gives more information about the intervention effect and so greater power than stated above. Our calculations assume an intracluster correlation (ICC) of 0.02, which is not based on published data. We believe that our power calculations are likely to be conservative because any loss from a higher ICC will be more than offset by the gain from the cross-over design.

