**Methods and analysis:**

This protocol describes a cross-over cluster randomised controlled trial of APT, offered as an additional PN method, compared with standard PN. The trial is accompanied by an economic evaluation, transmission dynamic modelling and a qualitative process evaluation involving patients, partners and healthcare professionals. Clusters are 17 sexual health clinics in areas of England and Scotland with contrasting patient demographics. We will recruit 5440 heterosexual women and men with chlamydia, aged ≥16 years.

The primary outcome is the proportion of index patients testing positive for *C. trachomatis* 12-16 weeks after the PN consultation. Secondary outcomes include: proportion of sex partners treated; cost effectiveness; model-predicted chlamydia prevalence; experiences of APT.

The primary outcome analysis will be by intention-to-treat, fitting random effects logistic regression models that account for clustering of index patients within clinics and trial periods. The transmission dynamic model will be used to predict change in chlamydia prevalence following APT. The economic evaluation will use mathematical modelling outputs, taking a health service perspective. Qualitative data will be analysed using interpretative phenomenological analysis and framework analysis.

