### Statistical analysis

Analysis will be by intention-to-treat. For the primary, and other quantitative outcomes, we will fit random effects models with fixed effects for clinic and intervention condition, together with a random effect to acknowledge the clustering of index patients for each combination of clinic and for each period.^34^ The primary and key secondary outcomes are binary, so we will use logistic regression models. The intervention effect will be expressed as an OR with 95% CI. Models for secondary outcomes with outcomes quantified for each sexual contact will include additional random effects for the index patient.

We anticipate loss to follow-up of around 40% of participants, raising potential concerns over bias. Before conducting our analysis of the primary outcome we will analyse predictors of follow-up from among a prespecified list of characteristics of the index patients that will be recorded at baseline and which are considered to be likely predictors of the primary outcome. In the primary analysis of the primary outcome we will include these as covariates in our regression model along with any other key predictors of the outcome. This approach should reduce bias from loss to follow-up but we will also conduct further sensitivity analyses based on multiple imputation in which we will allow those lost to follow-up to be more, and then less, likely to be chlamydia positive at 3 months than those not lost to follow-up with the same baseline covariates. These sensitivity analyses will follow the approach of Carpenter *et al*,^35^ to assess the robustness of our conclusions to different prespecified assumptions about missing data.

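### The stated 80% and 82% power for the primary outcome do not follow from all the protocol's own inputs; with the 60% re-test rate applied, the parallel-cluster figures are about 72–74% and 75–77%

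*Protocol article*

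**What the plan says.** All of this is in the Sample size section of the protocol article, unless noted.

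- Recruitment: the calculation rests on "recruiting an average of 160 index patients per clinic per trial phase" in 17 clinics (5440 in total), with a coefficient of variation of 0.5 in the number recruited.
- Patients in the primary analysis: "We expect that 50% of recruited patients (80 per clinic per phase and 2720 total) will contribute to the analysis of the primary outcome". The only reason given is that the analysis is restricted to patients with chlamydia detected at baseline.
- Re-testing: the next sentence adds a separate assumption, "We assume that 60% of index patients will provide a repeat sample". The Statistical analysis section likewise anticipates about 40% loss to follow-up.
- Power: "This sample size provides 80% power (at the 5% significance level") for 10% to 5%, 82% for 25% to 17%, and 87% for a rise from 60% to 70% in index patients with at least one partner treated.
- Method: the calculations were "performed as if the trial were a standard cluster RCT with 17 clinics in each arm", with an ICC of 0.02 that the authors say has no published source.
- Reserve: the authors believe the figures are likely to be conservative because "any loss from a higher ICC will be more than offset by the gain from the cross-over design".

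**The concern.** A patient who gives no repeat sample has no observed primary outcome. The halving from 160 to 80 deals with baseline positivity, and the 60% is a further reduction. Taken together they leave 80 × 0.60 = 48 patients per clinic-phase, so 2720 cannot be the number with a primary outcome.

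Two things are at stake. The power and the analysable number are the figures a reader uses to judge how informative a null result would be. The claim of conservatism also treats the cross-over gain as a free reserve against a higher ICC. If the stated power already leaves out the 40% loss, part of that reserve is spent before any higher ICC is considered.

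**Working it through.** **Inputs (protocol article, Sample size):** 17 clinics per arm, treated as a parallel cluster trial; ICC ρ = 0.02; CV = 0.5; m = 80 per clinic-phase without the re-test rate, or 48 with it. Significance is 5%. Sidedness is not stated; I take it as two-sided, in line with the Statistical analysis section ("The intervention effect will be expressed as an OR with 95% CI").

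**Formulas**

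- Design effect: DE = 1 + ((1 + CV²)m − 1)ρ
- Effective number per arm: n = 17m/DE
- Standard error: SE = √[(p₁(1−p₁) + p₂(1−p₂))/n]
- Power: from δ/SE, where δ = |p₁ − p₂|, by non-central t with 2 × (17 − 1) = 32 df, or by the normal approximation Φ(δ/SE − 1.96)

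**Step 1: reproduce the stated figures (m = 80).** DE = 1 + (1.25 × 80 − 1) × 0.02 = 2.98, and n = 1360/2.98 = 456. The ratios δ/SE are 2.88, 2.98 and 3.18. The t version gives 79.8%, 82.4% and 87.0%, which round to all three stated values.

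**Step 2: apply the 60% (m = 48).** There are 17 × 48 = 816 patients per arm and 1632 in total. DE = 1 + (1.25 × 48 − 1) × 0.02 = 2.18, and n = 816/2.18 = 374.

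- 10% v 5%: SE = √(0.1375/374) = 0.0192, and δ/SE = 0.05/0.0192 = 2.61. Power is 71.6% (t) or 74.2% (normal).
- 25% v 17%: SE = √(0.3286/374) = 0.0296, and δ/SE = 0.08/0.0296 = 2.70. Power is 74.5% (t) or 77.0% (normal).

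A pooled variance in the normal version gives 73.9% and 76.7%.

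**Step 3: try other routes to the stated figures.**

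| Inputs | 10→5% | 25→17% | 60→70% |
|---|---|---|---|
| Stated in the article | 80 | 82 | 87 |
| m = 80, CV 0.5, t | 79.8 | 82.4 | 87.0 |
| m = 48, CV dropped (DE 1.94), normal | 79.0 | 81.7 | 86.4 |
| m = 48, CV 0.5, one-sided 5%, t | 81.8 | 84.1 | 88.0 |

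Other two-sided variants at m = 48 with CV 0.5 (unpooled, arcsine, log odds ratio, continuity correction, optimal weights) give 69–77% and 74–79%.

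**Step 4: what the cross-over must supply.** Let c be the ratio of between-period to within-period ICC. The article gives no value, so every c below is an assumption, as is the ICC of 0.05. With m′ = 1.25 × 48 = 60, DE = 1 + 59ρ − 60ρc. This takes each clinic's size to be alike in the two periods. The t version uses 15 df (17 clinics, less one each for the intervention and period effects).

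| ICC | c | DE | Power 10→5%, normal | t, 15 df |
|---|---|---|---|---|
| 0.02 | 0.25 | 1.88 | 80% | 75% |
| 0.02 | 0.45 | 1.64 | 85% | 80% |
| 0.02 | 0.5 | 1.58 | 87% | 82% |
| 0.05 | 0.5 | 2.45 | 69% | 63% |
| 0.05 | 0.8 | 1.55 | 87% | 82% |

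At ICC 0.02, 80% is reached at c of about 0.25 (normal) or 0.45 (t). At ICC 0.05, whether the stated 80% is kept depends on c.

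**The case against.** The best reply is that the figures are declared to be a parallel-design approximation and that the section says the cross-over gives more power than stated. That stands. A reader might infer from the lower figures that the trial is underpowered, and the documents do not support this: at ICC 0.02 a moderate between-period correlation brings power to 80% or above. The shortfall is in the approximation as stated.

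A second reply is that the omitted input is inferred. This is also fair. Keeping the 60% and dropping the CV comes within about a point of all three figures, so it cannot be said that only an omitted re-test rate explains them. The match at 80 per clinic-phase is closer, and either route leaves out a stated input.

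A third reply is that the statement on conservatism is worded as a belief, with the source of the ICC openly qualified, and that it holds under some values (ICC 0.05 with a ratio of 0.8 gives 82–87%). I accept that. The objection is that its truth depends on a quantity the section never mentions.

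The 50% might also be read as already including attrition. The reason given for it, baseline positivity alone, rules that out.

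**Conclusion.** The point holds as an inconsistency between stated inputs and stated results. With every stated input used, parallel-cluster power is about 72–74% for 10% to 5% and 75–77% for 25% to 17%, about 5 to 8 points below the stated 80% and 82%. The number expected to provide the primary outcome is about 1632; the 2720 stated is 1.67 times that. These results assume a two-sided 5% test and the usual design effect for unequal cluster sizes.

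The most likely cause is that the 60% was not applied. The cross-over may well restore the power, but it has to make up this shortfall first, so the assurance about a higher ICC is conditional on an unstated between-period correlation.

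A reader might also infer that the 87% for partner treatment is too high by a similar amount. The documents do not support that. The 60% refers to the repeat sample at 12–16 weeks, whereas partner treatment is ascertained at the 2-week call, for which no response rate is given.

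**What to change.** In the Sample size section:

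1. Say that about 2720 recruited patients are expected to be chlamydia-positive at baseline, and that about 1632 of them (48 per clinic-phase, 816 per arm) are expected to provide the primary outcome.
2. Restate the parallel-cluster power as about 72–74% (10% to 5%) and 75–77% (25% to 17%), naming the test used. If the original calculation did apply the 60%, say which other input differed.
3. Make the sentence on conservatism conditional on the between-period correlation it needs. Show cross-over power for a few values labelled as assumptions, for example ICC 0.02 and 0.05 with ratios of 0.25, 0.5 and 0.8.

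The cost is a change of wording and a short calculation. The stated power becomes slightly less favourable. Recruitment, design and analysis stay as they are.

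### The power is called conservative because the cross-over will outweigh any higher ICC; this is true only if ICC minus the between-period correlation stays at or below about 0.02

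*Protocol article*

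**What the plan says.** The Sample size section of the protocol article states that its calculations were "performed as if the trial were a standard cluster RCT with 17 clinics in each arm". It gives 80% power for a fall from 10% to 5%, 82% for 25% to 17%, and 87% for the key secondary outcome (60% to 70%). On the correlation it is open: "Our calculations assume an intracluster correlation (ICC) of 0.02, which is not based on published data". It then says that the cross-over yields more power than stated, and that the figures are probably conservative because "any loss from a higher ICC will be more than offset by the gain from the cross-over design". It names no between-period correlation and no upper limit for the ICC.

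The Statistical analysis section plans fixed effects for clinic and intervention condition, with "a random effect to acknowledge the clustering of index patients for each combination of clinic and for each period".

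**The concern.** A cross-over of clusters gains precision because each clinic is its own control. Only the part of the clinic effect that is the same in both periods cancels. Whatever differs between a clinic's two periods stays in the treatment comparison, and for a given degree of persistence it grows in proportion to the ICC. A higher ICC is therefore offset only if most of it persists from one period to the next. The planned clinic-by-period random effect allows for persistence that is less than complete.

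The sentence is the only protection offered for an ICC that the authors say is unsupported. A reader who accepts it will take 80% and 82% as safe against a wrong ICC. If the ICC is higher and persistence only moderate, the real power is lower, and a null result could be given more weight than the planned precision justifies.

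**Working it through.** **Inputs from the Sample size section.** 17 clinics; 160 recruited per clinic per phase; 50% chlamydia-positive at baseline, so m = 80; 60% giving a repeat sample, so 80 x 0.6 = 48; coefficient of variation of cluster size (CV) 0.5, so 1 + CV² = 1.25; ICC 0.02; 5% significance, taken as two-sided.

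**Assumed, because not stated.** ICC values above 0.02, the ratio IPC/ICC, and the degrees of freedom (df) of the test. Each range below runs from a noncentral t with 16 df to the normal approximation.

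**Formulas.** Effective number per condition n = 17m/DE. Power follows from |p1 − p2| / sqrt[(p1(1 − p1) + p2(1 − p2))/n], with unpooled variance.

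- Parallel: DE = 1 + (1.25m − 1) x ICC
- Cross-over: DE = 1 + (1.25m − 1) x ICC − 1.25m x IPC

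**Step 1: the printed figures.** With m = 80 and ICC 0.02, parallel DE = 1 + 99 x 0.02 = 2.98 and n = 1360/2.98 = 456. With t on 32 df the power is 79.8%, 82.4% and 87.0%, against the printed 80%, 82% and 87%. The normal approximation gives 82.1% and 84.6% for the two primary scenarios. So m = 80 is the number that reproduces the print. With m = 48, DE = 1 + 59 x 0.02 = 2.18, n = 816/2.18 = 374, and the primary figures are 71.6-74.2% and 74.5-77.0% (32 df to normal).

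**Step 2: when the offset works.** Setting the cross-over DE equal to the parallel DE at ICC 0.02 gives

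ICC − IPC = 0.02 + (ICC − 0.02)/(1.25m).

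The last term is tiny. At m = 80 and ICC 0.05 it is 0.03/100 = 0.0003, so the condition is ICC − IPC ≤ 0.0203, that is IPC ≥ 0.0297 or IPC/ICC ≥ 0.59. At ICC 0.03 the ratio must be at least 0.33, and at ICC 0.10 at least 0.79. These break-even values compare design effects only; fewer df make them slightly stricter.

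**Step 3: one case in full.** ICC 0.05, IPC 0.025, m = 80: DE = 1 + 99 x 0.05 − 100 x 0.025 = 3.45, and n = 1360/3.45 = 394. For 10% v 5% the standard error is sqrt(0.1375/394) = 0.0187, the ratio is 0.05/0.0187 = 2.68, and normal power is Φ(2.68 − 1.96) = 76%. With 16 df it is 71%.

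**Step 4: the range.**

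| m | ICC | IPC/ICC | DE | 10% v 5% | 25% v 17% |
|---|---|---|---|---|---|
| 80 | 0.02 | 0 | 2.98 | 77.2-82.1% | 79.9-84.6% |
| 80 | 0.02 | 0.5 | 1.98 | 91.2-94.2% | 92.9-95.5% |
| 80 | 0.03 | 0.5 | 2.47 | 84.4-88.6% | 86.7-90.6% |
| 80 | 0.05 | 0.5 | 3.45 | 71.0-76.3% | 73.9-79.1% |
| 80 | 0.05 | 0.8 | 1.95 | 91.6-94.5% | 93.3-95.8% |
| 80 | 0.10 | 0.5 | 5.90 | 48.6-53.5% | 51.2-56.3% |
| 80 | 0.10 | 0.8 | 2.90 | 78.3-83.1% | 81.0-85.6% |
| 48 | 0.05 | 0.5 | 2.45 | 63.7-69.2% | 66.7-72.1% |
| 48 | 0.05 | 0.8 | 1.55 | 82.7-87.2% | 85.2-89.3% |

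In the first row the design effect equals the parallel one. The 2-3 points below the printed figures at its lower end come only from having 16 rather than 32 df.

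**The case against.** The protocol presents its conclusion as a belief and as likely, and it discloses both the parallel formula and the weak basis of the ICC. That is fair, and a reader should not infer that it guarantees a floor. But the hedge applies to the conclusion; the reason beneath it covers every higher ICC.

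A stronger case is that the losses need an ICC well above plan together with modest persistence. At ICC 0.05, ratio 0.5 and a 10% risk, a clinic's true risk would change between periods with a standard deviation of sqrt(2 x 0.05 x 0.09 x 0.5) = 0.067. That is 6.7 percentage points, more than the 5-point target effect. The Trial timeline section has the same clinics in near-adjacent six-month phases, and the Settings section selects clinics for contrasting demographics; both favour persistence. Covariate adjustment may also reduce the clinic-by-period variation. All this makes the severe rows less plausible. It does not exclude the moderate ones, and the documents give no figure that would.

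Three stronger readings are tempting and not supported:

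- That the parallel formula is a mistake. It is disclosed, and at ICC 0.02 the cross-over does not lower power apart from the df effect at IPC 0.
- That the trial is underpowered. This depends on an ICC and an IPC that the documents do not give.
- That the analysis model contradicts the sample size section. The clinic-by-period effect is a sound safeguard. The planned 95% CI will also show any extra imprecision, which limits the risk of misreading a null result.

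**Conclusion.** The point holds as a correction to one stated reason. The cross-over offsets a higher ICC only while ICC minus IPC is at or below about 0.02. Within that limit the printed figures stand at 80 per clinic-phase, apart from the df effect; outside it they do not. At ICC 0.05 and ratio 0.5 the shortfall from the printed figures is about 4-9 points for 10% v 5% (71-76% against 80%) and 3-8 points for 25% v 17% (74-79% against 82%). At 48 per clinic-phase the same case gives 64-69% and 67-72%, but part of that gap comes from the smaller number analysed. At ratio 0.8 and ICC 0.05 there is no shortfall at either number. The mechanism follows from the planned model; the sizes rest on assumed ICC, IPC and df.

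**What to change.** In the Sample size section, delete the reason that any loss from a higher ICC is more than offset, or make it conditional on ICC minus IPC being no more than about 0.02.

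Restate the power with the cluster cross-over design effect, 1 + ((1 + CV²)m − 1) x ICC − (1 + CV²) x m x IPC, over a short range of ICC and IPC/ICC. Show it for 48 as well as 80 analysed per clinic-phase, and state the df.

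Report the estimated clinic-by-period variance with the primary result. A between-clinic variance cannot be asked for, because clinic is a fixed effect in the planned model.

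The cost is one sentence changed and a short table. Recruitment and conduct are unaffected. The drawback is that the stated power becomes conditional and, in part of the range, less favourable.
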